*** Maternal outcomes***					
	Maternal weight	Continuous (in kg)	Measured using calibrated scale	At enrollment (between 9–< 14-weeks gestation), 20–26-weeks gestation, 30–34-weeks gestation, and during labor/delivery	Mean (SD)
	Maternal weight gain	Categorical (inadequate/adequate/excessive)	IOM guidelines and calculated based on maternal weight at labor/delivery-maternal weight at enrollment	At enrollment (between 9–< 14 weeks gestation), 20–26-weeks gestation, 30–34-weeks gestation, and during labor/delivery	Proportions
	Maternal prenatal and postnatal depression	Continuous and binary	Edinburgh Postnatal Depression Scale (EPDS) (range 0–30; 12 or higher defining maternal depression)	At 6 weeks and 6 months of child age	Mean (SD), prevalence above threshold
	Maternal cortisol concentration	Continuous	Cortisol concentration from maternal hair samples	Between 9–< 14 weeks, 20–26 weeks, and 30–34 weeks gestational ages, at time of birth, and at 6 weeks and 6-months post birth	Mean (SD)
	Minimum Dietary Diversity for Women (MDD-W)	Binary	Diet Quality Questionnaire (DQQ) will be used to generate MDD-W, used here as meeting the validated threshold or not 0–10 scale, where a higher score indicates more diversity (better) with threshold of having at least 5 to have met minimum requirements (coded as 0 for not having met/1 for having met MDD)	Between 9–< 14 weeks, 20–26 weeks, and 30–34 weeks of gestational ages, at time of birth, and at 6-week and 6-month post-birth	Proportion
	Dietary diversity score	Continuous	Sum of score from different food groups 0–10	Between 9– < 14 weeks, 20–26 weeks, and 30–34 weeks of gestational ages, at time of birth, and at 6-week and 6-month post-birth	Mean DDS
	Maternal hemoglobin	Continuous/categorical	Trimester-specific WHO cutoffs	Between 9– < 14 weeks, 20–26 weeks, and 30–34 weeks of gestational ages, at time of birth, and at 6-week and 6-month post-birth	Mean (SD), anemia prevalence by trimester
	Biomarkers of micronutrient status, growth factors, systemic inflammation, environmental enteric dysfunction, metabolomics, choline, and lipid panel (including HDL and LDL cholesterol)	Continuous	Measured using whole blood or serum samples among women and infants	Between 9– < 14 weeks, 20–26 weeks, and 30–34 weeks of gestational ages, at time of birth, and at 6-week and 6-month post-birth	Mean (SD)
	Maternal blood pressure	Continuous/categorical	Diastolic and systolic blood pressure	Between 9–< 14 weeks, 20–26 weeks, and 30–34 weeks of gestational ages, at time of birth, and at 6-week and 6-month post-birth	Mean (SD), prevalence of hypertension per protocol

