*** Other outcomes***					
	Thalamus length, width, and transverse	Continuous (in cm)	Ultrasound measurement	Between 20–26 weeks and 30–34-week gestational ages	Mean (SD)
	Consumption of ASF	Score (0–4)	Based on DQQ questionnaire	Between 9– < 14 weeks, 20–26 weeks, and 30–34 weeks of gestational ages, at time of birth, and at 6-week and 6-month post-birth	Mean (SD)
	Child’s motor, cognitive, socio-emotional, and language development domain specific scores	Domain-specific scores	Based on CREDI long form	6 months of age	Mean (SD)

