## Statistical methods

### Statistical methods for primary and secondary outcomes {20a}

The primary analysis of the RCT will be based on a modified intention-to-treat (ITT) principle. This trial is designed to formally test the mean difference in the primary outcome of birth LAZ between the treatment arm and the control arm (T1–T2). All women who have a live birth and for whom childbirth length is measured within 72 h will be included in the analysis of the primary outcome. Cases for whom primary outcome data are not available (missing) will not be included in analyses. Descriptive analysis, such as frequency and percentages, will be reported for categorical variables, while means, standard deviation, and quartiles will be reported for continuous variables.

For secondary outcomes, the two-sample *t*-test will be used if the outcome is normally distributed with or without transformation, and the Wilcoxon rank-sum test will be used if the outcome is not normally distributed, where normality will be assessed using the Shapiro–Wilk test and Q-Q plot. Kruskal–Wallis and two-sample rank sum tests will be used if their distribution is non-normal. For both primary and secondary outcomes at birth, exploratory analyses will be conducted using multivariable linear or logistic regression models to adjust for potential confounders (such as baseline SES, gestational age at birth, mother’s education, mother’s age, and dietary diversity) that may be imbalanced across treatment arms. Imbalance of baseline factors may occur as a post-randomization selection bias or by chance alone. Post-randomization selection bias is possible, especially given that participants are not blinded. If this occurs, it will be crucial to adjust for imbalanced confounders in all regression analyses. Village-level heterogeneity will be considered using random effects. Spatial correlation in village-level random effects will be adjusted for if spatial clustering patterns in the outcomes are present. For longitudinal outcomes such as head circumference, linear or generalized linear mixed models will be used to account for heterogeneity in the intercept and slope of growth.

All statistical analyses will be conducted using R and Stata. The statistical significance for regression models will be set at *p* < 0.05 without further adjustment for multiple comparisons.

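### The enrolment value of eight maternal and diet outcomes is given no baseline role, and the stated two-sample test would leave its precision unused

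*Protocol article*

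**What the plan says.** **Timepoints.** In Outcomes {12}, Table 1, the timepoint entry for maternal weight is "At enrollment (between 9–< 14-weeks gestation), 20–26-weeks gestation, 30–34-weeks gestation, and during labor/delivery". For hair cortisol it is "Between 9–< 14 weeks, 20–26 weeks, and 30–34 weeks gestational ages, at time of birth, and at 6 weeks and 6-months post birth". Blood pressure has "Between 9–< 14 weeks, 20–26 weeks, and 30–34 weeks of gestational ages, at time of birth, and at 6-week and 6-month post-birth", and MDD-W, dietary diversity score, haemoglobin and biomarkers carry the same six visits. Under Other outcomes, the ASF score does too: "Between 9– < 14 weeks, 20–26 weeks, and 30–34 weeks of gestational ages, at time of birth, and at 6-week and 6-month post-birth". That makes eight rows. A ninth, maternal weight gain, also lists enrolment, but there the enrolment value is part of the definition: "IOM guidelines and calculated based on maternal weight at labor/delivery-maternal weight at enrollment".

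**Order of events.** The allocation section places randomisation after enrolment. Section {18a} calls the enrolment blood and hair samples baseline samples; Table 1 does not.

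**Analysis.** Section {20a} says that for secondary outcomes the two-sample t-test "will be used if the outcome is normally distributed with or without transformation", with the rank-sum test otherwise. On covariates it says: "For both primary and secondary outcomes at birth, exploratory analyses will be conducted using multivariable linear or logistic regression models". The covariates given as examples include dietary diversity, but not weight, haemoglobin, blood pressure or cortisol at enrolment. The same section then assigns longitudinal outcomes to linear or generalised linear mixed models that allow for varying intercepts and growth slopes, with head circumference as its example.

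**The concern.** A value measured before allocation cannot carry a treatment effect. Its use in the analysis is to explain variation between women at the later visits. Table 1 puts it on the same footing as the later visits, and the test named for secondary outcomes has no place for it. Read together, these two statements lead an analyst to compare raw later values between arms.

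What is at stake is precision. The maternal questions in Hypotheses and objectives {7} include blood pressure and anaemia. Their intervals could be wider than necessary although the enrolment values needed to narrow them are scheduled for collection.

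**Working it through.** **1. The plan's own figure.** Sample size {14} gives a difference of 0.18 in LAZ, 80% power, one-sided 5% and 20% attrition. With SD = 1 (assumed; not stated), n = 2 × (1.645 + 0.842)² / 0.18² = 382 per arm, and 382 / 0.8 = 478. The stated 478 is reproduced. It was set for LAZ; no sample size or power is stated for the maternal outcomes.

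**2. Effect of adjusting for the enrolment value.** For a continuous outcome with correlation ρ between the enrolment and later value, adjustment multiplies the residual variance by (1 − ρ²), the standard error by √(1 − ρ²), and the effective sample size by 1/(1 − ρ²). The protocol gives no ρ, so a range is assumed. For power I use 382 per arm, a two-sided 5% test and, purely as an illustration, a standardised difference of 0.18.

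| ρ | Variance removed | SE multiplier | Equivalent gain in women | Power, 382 per arm |
|---|---|---|---|---|
| no adjustment | 0 | 1 | 0 | 70.1% |
| 0.3 | 9% | 0.95 | 10% | 74.1% |
| 0.5 | 25% | 0.87 | 33% | 81.9% |
| 0.7 | 49% | 0.71 | 96% | 93.6% |
| 0.9 | 81% | 0.44 | 426% | over 99% |

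The first four columns do not depend on the sample size. During pregnancy more than 382 women per arm may still be in follow-up. At the upper limit of 478, power is 79.5% unadjusted and 83.1%, 89.5% and 97.4% at ρ = 0.3, 0.5 and 0.7.

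**3. Weight in kg.** Assume SD 10 kg, a true difference of 1 kg at 30–34 weeks, 382 per arm, and ρ of 0.85, 0.90 or 0.95.

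- Unadjusted: SE = 10 × √(2/382) = 0.72 kg; power 28%.
- Adjusted: SE = 0.38, 0.32 or 0.23 kg; power 75%, 89% or 99%.
- With SD 8 kg: 41% against 91%, 98% and nearly 100%. With SD 12 kg: 21% against 59%, 75% and 96%.

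None of these weight inputs is in the protocol.

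**4. If the mixed-model sentence applies instead.** The result depends on how enrolment enters. A model with a common baseline mean recovers the gain above. If enrolment is an ordinary response and the model has one arm term, a visit with no effect is averaged in. With complete data, equal visit weights and a constant effect from the second visit on, the estimate shrinks to 3/4 of the true effect for weight (four visits) and 5/6 for the measures with six visits. The protocol does not say which model is meant.

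**The case against.** **The mixed-model sentence.** This is the strongest counter-argument. Head circumference is only an example there, and maternal weight, haemoglobin, blood pressure, cortisol and diet are all measured repeatedly. A mixed model with enrolment as its first response uses that value, and listing enrolment among the timepoints fits such a model. So it cannot be said that the plan ignores the enrolment value. What the objection does not settle is which of the two methods these outcomes receive, or what role enrolment has. The sentence is aimed at growth intercepts and slopes and assigns no maternal outcome to the model.

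**Baseline comparisons as outcomes.** A reader might infer from Table 1 that the arms are to be tested at enrolment and chance differences reported as results. The documents do not support that. The table gives timepoints and aggregations, not tests, and no section plans an arm comparison at enrolment.

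**The weight question.** A reader might also take the weight example as the plan's answer to its first maternal question. That question concerns weight gain, which already subtracts the enrolment weight. This stands: the kg illustration applies only to the separate maternal-weight row.

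**Imbalance.** Section {20a} also asks for adjustment for imbalanced confounders in regression analyses. That is conditional on imbalance, whereas the gain in precision from a prognostic baseline value does not require any.

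**Level of detail.** The covariates of each secondary model commonly belong in the SAP, which is not shown, and their absence here would be no finding. The point rests on what the article does state: a test without a baseline term, beside a timepoint list that treats enrolment as an outcome visit.

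**Conclusion.** The point holds as a matter of precision and clarity in secondary outcomes. Table 1 does not mark the enrolment visit as baseline for eight rows. Section {20a} names a test that cannot use the enrolment value, and a mixed model that might, without assigning these outcomes to either.

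If the two-sample test is applied to later values, the comparison of randomised arms remains unbiased. The cost is the residual variance that adjustment would have removed: 9%, 25% or 49% at ρ = 0.3, 0.5 or 0.7, and 72% to 90% for weight in kg if ρ is 0.85 to 0.95. At the low end this is minor (70% against 74% power in the illustration); for a stable measure it is large. All of this rests on assumed correlations, and the formula is for continuous outcomes, so it does not carry over directly to the binary MDD-W. That enrolment measurements precede the opening of the envelope is implied rather than spelled out. The primary LAZ analysis is not affected.

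**What to change.** 1. In Table 1, mark the 9 to <14 week visit as baseline, not an outcome timepoint, in the eight rows. Leave weight gain as a change from that baseline.
2. In {20a}, state that post-randomisation values of these outcomes are analysed by regression on arm, the woman's own enrolment value of the same measure and the gestational-age stratum (logistic regression for binary outcomes such as MDD-W). Alternatively, use a repeated-measures model with one baseline mean common to both arms. Either replaces the two-sample test for these rows, and the text should say which applies.

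The biomarker row covers women and infants; the change applies to the maternal values only, and only where the enrolment sample is assayed.

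The cost is a table edit and one or two sentences. Table 2 already schedules weight, blood pressure, blood, hair and the diet questionnaire at enrolment, so no new visit or sample is needed. Section {33} makes some biomarker assays depend on further funding, and its maternal examples start at the third trimester. For those markers, an enrolment assay would be an added laboratory cost.

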Does maternal egg consumption lead to improved birth outcomes when compared to birth outcomes of mothers who consume a typical diet (birth outcomes will include miscarriage, stillbirth, preterm births, low-birth weight, small-for-gestational age)?Does any observed effect of maternal egg consumption on birth outcomes (compared to typical diet) differ by child sex (male/female)?Does maternal egg consumption improve other child growth outcomes (including stunting, wasting, and underweight) at 6 months of age compared to a typical diet?Does maternal egg consumption lead to improved levels of micronutrients (iron, vitamin B12, vitamin A) in children at 6 months of age compared to a typical diet?Does maternal egg consumption lead to improved neurodevelopment in utero (as indicated by ultrasound-based measures) or during the first 6 months of life (head circumference, Hammersmith Neonatal Neurological Exam (HNNE), and Caregivers-Reported Early Development Instrument (CREDI) scores compared to typical diet?

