	Small vulnerable newborn status	Binary	Any of: SGA (< 10th), preterm (< 37 weeks), or low birthweight (< 2500 g)	Within 72 h of birth	Proportion
	Head circumference z-score	Continuous (z-score)	INTERGROWTH 21st growth standards	Within 72 h of birth	Mean (SD)
* Infant measurements*	Prevalence of stunting among infants	Binary	Length-for-age < −2 SD according to the WHO Multicenter Growth Reference Study standards	At 6 weeks and 6 months of age	Percentage
	Infant weight-for-age z score	Continuous (z-score)	WHO Child Growth Standards	At 6 weeks and 6 months of age	Mean (SD)
	Prevalence of underweight	Binary	Weight-for-age < -2 SD according to the WHO Multicenter Growth Reference Study standards	At 6 weeks and 6 months of age	Percentage
	Child neurodevelopment- HNNE	Continuous/domain score	Hammersmith Neonatal Neurological Examination (HNNE)	At 6 weeks of age	Domain and total scores
	Child neurodevelopment-CREDI	Continuous	Caregiver-Reported Early Childhood Development Instrument (CREDI) score (long form)	At 6 months of age	Domain-specific scores

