**Baseline and follow-up surveys**						
Mother’s anthropometry	X	X	X	X*	X	X
Mother’s clinical assessment (blood pressure and current health condition)	X	X	X			
Mother’s medical and obstetrics history	X					
Socioeconomic status	X					X
Smoking and alcohol consumption	X	X	X		X	X
Dietary Quality Questionnaire (DQQ)	X	X	X		X	X
Household Food Security (HFIAS)	X					X
Water and sanitation	X					
Pregnancy history	X					
Malaria prevention	X					
Physical activity	X	X	X			
Depression (EPDS)		X	X		X	X
Intention to breastfeed		X	X			
Immediate feeding				X		
Gender-based violence					X	X

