### Sample size {14}

Nutritional interventions during pregnancy have yielded mixed results in their impact on LAZ at birth. Previously reported mean difference in LAZ ranges from 0.12 [2, 18] to 0.29 [12, 17]. Notably, the 0.29 effect size observed by Dhaded et al. [12] was associated with nutritional supplementation initiated prior to conception, whereas supplementation beginning in the first trimester yielded a smaller effect size of 0.21. Considering most studies report an effect size below 0.20 and based on the available literature on other food supplementation as found in some literature review papers by Imdad and Bhutta [23] and Stevens et al. [46], we hypothesize a mean difference of 0.18 in LAZ to be both a reasonable and clinically meaningful effect size. As such, we calculate the sample size based on testing two hypotheses simultaneously:$$H0:d1\leq0\;vs.\;Ha:d1>0$$

For our hypothesized effect size, the sample size required with 20% attrition (accounting for pregnancy loss, stillbirths, and loss of follow-up) to attain an 80% marginal power with a 5% level of significance was 478 per arm, based on a two sample one-sided test. Thus, we aim to enroll an overall sample of 956 women in the proposed study. Sample calculation was performed using “pwr” package [5] in RStudio.

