### Plans for collection, laboratory evaluation, and storage of biological specimens for genetic or molecular analysis in this trial/future use {33}

As described above, maternal blood samples will be drawn at enrollment, second trimester, third trimester, and 6-week and 6-month visits. A total of 12-ml blood will be drawn from women and will be stored in three tubes (4 ml each). Maternal hemoglobin concentrations will be measured at the point of care using a Sysmex poch-100i automated hematology analyzer. Infant blood samples will be drawn at 6 weeks and 6 months of age. Drawn blood from the mother and infant will be kept in a cooler box with ice packs and, after isolating the serum, will be put into a −20 °C cooler within 8 h of collection. Within 7 days of collection, the sample will be transferred to Kigali for longer-term storage in −80 °C freezers at the University of Rwanda or Rwanda Biomedical Center. From the blood samples collected, a lipid (LDL and HDL cholesterol, triglycerides, HDLC4) and glucose panel will be measured among women at first, second, and third trimester visits and post-birth visits at 6 weeks and 6 months. These tests will be done at the *Nyagatare* district hospital using a *Roche Cobas c311* chemical analyzer.

The present study has approval for blood draws and long-term storage, but plans for further analyses are pending additional funding. Examples include the following:Maternal serum biomarkers of nutritional status and inflammation at third trimester and at 6-week and 6-month postpartum. These may include but are not limited to soluble transferrin receptor (sTfR), ferritin, retinol-binding protein (RBP), C-reactive protein (CRP), and alpha-1-acid glycoprotein (AGP).Child serum biomarkers of nutritional status and inflammation at birth and 6-week and 6-month postpartum. Pending funding, these may include but are not limited to sTfR, ferritin, RBP, CRP, and AGP.

Hair samples will be collected from women to assess cortisol levels, a hormone indicative of stress. Hair samples will be stored in zipped plastic bags at room temperature until transport for laboratory analysis.

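### Table 1 disagrees with the collection schedule on specific measures and visits, and after birth it declares length only as stunting and omits wasting

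*Protocol article*

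**What the plan says.** **Time points in Table 1.** MDD-W, dietary diversity score, hemoglobin, biomarkers, blood pressure and the ASF score are each listed at the three pregnancy visits and "at time of birth, and at 6-week and 6-month post-birth". Hair cortisol has the same pattern: "at time of birth, and at 6 weeks and 6-months post birth". The row for prenatal and postnatal depression gives 6 weeks and 6 months only.

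**What is scheduled.** Table 2 marks maternal blood, maternal hair and the DQQ at the three pregnancy visits, 6 weeks and 6 months. Its blood pressure row, "clinical assessment (blood pressure and current health condition", is marked at the three pregnancy visits only. EPDS is marked at 20–26 weeks, 30–34 weeks, 6 weeks and 6 months. The section on biological specimens {33} says that "maternal blood samples will be drawn at enrollment, second trimester, third trimester, and 6-week and 6-month visits".

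**Growth after birth.** Hypotheses and objectives {7} makes child growth at birth, 6 weeks and 6 months the main objective. It also asks about other growth outcomes, "including stunting, wasting, and underweight) at 6 months of age". For length at 6 weeks and 6 months, Table 1 has one row, "Prevalence of stunting among infants", a binary outcome. Weight-for-age at the same visits appears both as a z-score and as underweight. There is no wasting or weight-for-length row.

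**The concern.** Table 1 is where this document fixes the outcomes, their metrics and their time points. Where it names a time point at which the measure is not scheduled, that cell will be empty or will be dropped later without a stated reason. Where it leaves out data that are collected, someone must decide after the fact whether to report them. Regression models are tested at p < 0.05 without multiplicity adjustment, so a later decision to add infant LAZ, wasting or prenatal EPDS would look like selection.

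The length gap also has a statistical cost. Whether a gain in birth length persists is part of the stated main objective. A yes/no cut at −2 SD is a weak way to detect a shift in a mean, and it is the only declared form of length after birth.

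**Working it through.** **1. Time points side by side.**

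| Table 1 row | Birth in Table 1 | Birth in Table 2 | 6 weeks and 6 months |
|---|---|---|---|
| Hemoglobin, biomarkers | yes | no blood sample | maternal blood in both tables |
| Hair cortisol | yes | no hair sample | in both tables |
| MDD-W, dietary diversity, ASF score | yes | no DQQ | in both tables |
| Blood pressure | yes | no | Table 1 yes, Table 2 no |

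That makes seven rows with an unscheduled birth time point. Blood pressure has two further unscheduled time points.

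This is not an effect of broken table layout, because the text agrees with Table 2. The assessment section {18a} describes neonatal anthropometry at birth. It places maternal blood and hair at baseline, the two later pregnancy visits, 6 weeks and 6 months, and the DQQ at those same visits. It does not mention blood pressure at birth or postpartum.

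Two further mismatches concern biomarkers:
- Section {33} draws infant blood only at 6 weeks and 6 months, yet lists child serum biomarkers at birth as a possible analysis pending funding.
- Table 2 has a separate maternal biomarkers row marked in pregnancy only, while section {33} measures lipids and glucose in women at 6 weeks and 6 months as well.

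**2. The plan's own sample size.** The inputs from Sample size {14} are:
- effect: "we hypothesize a mean difference of 0.18 in LAZ to be both a reasonable and clinically meaningful effect size";
- operating characteristics: "to attain an 80% marginal power with a 5% level of significance was 478 per arm, based on a two sample one-sided test";
- attrition: 20%.

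The SD is not stated. SD = 1 is assumed here, and it reproduces the plan's figure:

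n = 2 × (1.645 + 0.842)² / 0.18² = 382 evaluable per arm, and 382 / 0.8 = 477.5, so 478 enrolled per arm. This matches.

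**3. Power for length after birth, with 382 evaluable per arm.** The assumptions are that the 0.18 SD shift persists, SD is 1, z-scores are normal, and the 20% attrition set for the birth outcome also holds later.

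*Continuous LAZ.* 0.18 / √(2/382) = 2.488. Power is Φ(2.488 − 1.645) = 80% one-sided and Φ(2.488 − 1.960) = 70% two-sided.

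*Stunting.* With control rate p₀, the treated rate is p₁ = Φ(Φ⁻¹(p₀) − 0.18). Power is Φ{[(p₀ − p₁)√382 − z√(2p̄(1 − p̄))] / √(p₀(1 − p₀) + p₁(1 − p₁))}, where p̄ is the mean of the two rates.

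| Control rate | Treated rate | Power, one-sided | Power, two-sided | Evaluable per arm for 80% one-sided | Efficiency (382 / that n) |
|---|---|---|---|---|---|
| 10% | 7.2% | 40% | 28% | 1,233 | 31% |
| 15% | 11.2% | 47% | 35% (34.5) | 969 | 39% |
| 20% | 15.4% | 52% | 39% | 831 | 46% |
| 30% | 24.1% | 58% | 46% | 690 | 55% |

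The document's only stunting rate is 30%, for children under 5 in the district. The lower rates are assumptions that cover a plausible range for infants. Both sidedness columns are shown because the document does not state the sidedness of the secondary tests.

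If the SD is larger, the power of continuous LAZ falls to 73% (SD 1.1) or 67% (SD 1.2) one-sided.

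**The case against.** The strongest reply is that these are mostly table mismatches, that they affect no primary result, and that the research questions can still be answered. Much of this stands, and it rules out several stronger readings.

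- *A reader might infer that nothing is collected at these visits, or that the outcomes cannot be produced.* The document does not support that. The birth, 6-week and 6-month visits collect other data. Hemoglobin, cortisol and the DQQ outcomes are scheduled at five of their six listed visits, and blood pressure at three. The objectives ask about blood pressure during pregnancy and anemia after birth, and both are covered.
- *A reader might infer that the main growth objective is underpowered.* The confirmatory test is continuous LAZ at birth, and its sample size reproduces. The protocol claims no power for later length.
- *A reader might infer that prenatal depression has no outcome.* The row is named for it and EPDS is collected in pregnancy. Only the time-point cell is incomplete.
- *A reader might say that dichotomising always discards most of the information.* At 30% stunting about 55% of the efficiency is kept.

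Stunting is also a national policy target, so there is no case for demoting it. Length is measured to 0.1 cm at both later visits, so no data are lost. The statistical methods section foresees mixed models for longitudinal outcomes, but its only example is head circumference, so infant LAZ is not declared there.

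It can also be said that an article condenses the full protocol. That excuses omissions, but it does not excuse two tables in the same article that contradict each other.

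**Conclusion.** The point holds in limited form. Seven Table 1 rows name a birth time point that the schedule does not contain. Blood pressure also names two postpartum time points that are not scheduled. The depression row omits the two pregnancy visits at which EPDS is collected. Length after birth is declared only as stunting, and wasting is missing although the objectives ask about it.

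The primary analysis is untouched. For the secondary question of whether a length gain persists, the declared binary outcome has 40–58% power one-sided (28–46% two-sided), against 80% (70%) for continuous LAZ from the same measurements. These figures rest on the assumed persistence of 0.18, SD 1, 382 evaluable per arm and control stunting of 10–30%. The direction of the comparison does not depend on the exact values, but its size does.

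**What to change.** - Add continuous WHO LAZ at 6 weeks and 6 months to Table 1, alongside stunting.
- Add weight-for-length z-score and wasting at 6 months.
- Add 20–26 and 30–34 weeks to the EPDS row.
- Reconcile the Table 1 time points with Table 2 and section {33}, and remove those at which the measure is not collected. For postpartum blood pressure, either schedule the reading at the existing visits or delete the time points.
- Do not simply strike the birth time point from the biomarker row. That row covers women and infants, so first settle whether child biomarkers at birth are intended, and align Table 2's pregnancy-only maternal biomarkers row with the postpartum blood tests.

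The cost is an amendment to the tables. Lengths, weights and EPDS are already collected, and enrollment is paused, so the timing is convenient. The downside is a few more secondary outcomes without multiplicity adjustment, which should be acknowledged when they are reported.
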